**Figure 2 Fig2:**
[figure not shown]
**DermLite lens attachment by 3Gen.**

Another key element of the study is the development of the photo repository where participants in the PAE + MD + TD arm will upload DermLite photographs for review. Images can be uploaded from participants’ phones/tablets or the study website. When participants upload a photograph to the repository, they are asked a series of questions including: (1) date the photo was taken, (2) if they had previously submitted a photo of that particular mole, mark or spot, (3) location of the mole, mark, or spot (with a drop down menu of options to select from), and, (4) symptoms of the mole, mark or spot (with a drop down menu of options to select from). The photos will be reviewed by study staff to ensure acceptable quality and content before they are sent to the study dermatologist. The photographs will be reviewed by the study dermatologist and an individualized report and status will be generated for each photograph (for example, (a) morphology is suggestive of a benign lesion; (b) morphology is indeterminate and management will require evaluation and follow-up with a physician; (c) lesion has morphologic features suggestive of malignancy; and, (d) image is of insufficient quality - photograph needs to be retaken). The report will be sent to the corresponding participant’s physician. The participant will be instructed to contact his or her identified physician to receive the teledermoscopy report and to discuss follow-up measures.

### Tracking and follow-up

All participants will utilize a unique username and password to access the website. We are able to collect data on participants’ paths through the site, the amount of time spent on each page, total session time, and use of various components. Analytic software will be used to track aggregate website statistics. Participants will also be asked on the 12- and 18-month surveys to report their use of and experiences with the website. Study staff will utilize the photo repository database to track the number of photographs sent per participant as well as the time interval from the date the photograph was sent to the date that a report was processed. Additionally, on the 12- and 18-month surveys, participants will be asked if they brought the appointment checklist to their physician visits and the frequency with which they examined their skin, but found lesions of little concern, and chose not to use teledermoscopy (PAE + MD + TD arm only).

### Outcomes and measurements

#### Thorough skin self-examination (TSSE)

Self-report of TSSE has been validated [22,48], and as an outcome will be defined as performing at least one TSSE during the 2 months prior to the 12- and 18-month follow-up assessments. Participants will be asked how often in the prior 2 months they had performed a TSSE and if, in the 2 months prior to survey completion, they carefully examined each of 9 areas of the body (‘the front of your body from the waist up’, ‘the front of your thighs and legs’, ‘the bottom of your feet’, ‘your calves’, ‘the backs of your thighs’, ‘your buttocks’, ‘the lower parts of your back’, ‘your upper back’, and ‘your scalp’) [22,48]. Those who respond ‘yes’ to each of these nine questions will be considered to have performed TSSE.

#### Physician skin cancer examination

Completion of a physician skin exam will be assessed at baseline, 12 months, and 18 months by participant report and chart review. At each assessment time point, participants will be asked: ‘During the past 12 months, has your regular health care provider or your dermatologist carefully examined your whole body for any sign of skin cancer’, and whether the examination took place during a routinely scheduled visit or was prompted by a request from the participant. Participants’ self-report will be corroborated via chart review using a standard form submitted to the provider to assess each of the following: a skin examination has been performed, a skin self-exam has been recommended, and completion of a follow-up visit and the date for such a visit has been reported. Physician offices will be incentivized a total of $25.00 for review of the participant’s medical record related to the skin exam to be completed after the participant completes his/her 18-month survey.

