### Primary study outcomes

Primary study outcomes will be measured at baseline, 12- and 18-months and include the following: (1) at least 1 thorough skin self-examination completed by the patient in the 2 months prior to both the 12- and 18-month survey; (2) at least 1 physician skin examination prior to 18-month survey; and, (3) reduction of the time interval between the first finding of a suspect lesion and a diagnostic visit.

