### Recruitment

The study protocol was reviewed and approved by the Institutional Review Board of Harvard TH Chan School of Public Health (approval number: IRB12-0002). Participants who meet study eligibility criteria will be invited to enroll. The invitation packet includes the invitation letter, Health Insurance Portability and Accountability Act (HIPAA) authorization, consent form, and the baseline survey.

Upon receipt of the completed survey and HIPAA authorization, the participant is officially enrolled in the study and randomized to one of three study arms. Within 7 days of randomization, each participant receives an enrollment packet that includes: a letter welcoming them to the study; print materials about their skin cancer risk, how to conduct skin self-examinations, an appointment checklist providing tips and suggestions about physician skin examinations for participants to reference when they go to see their doctor; and details about how to access the study website. Participants in Arm 3 also receive the dermatoscope and instructions for attaching it to their smartphone, using it, and uploading photos to the photo repository.

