**Table 1 Tab1:** **Core intervention components of the three arms**

	**Intervention strategy**	**Content**	**Mediating variables addressed**
PAE	• 14 text messages	• 1 text: welcoming participants to the study	• PAM components:
		• 12 texts: reminders to conduct thorough skin self-examinations (TSSE), prompts to see a health care provider (HCP) for suspect lesions, messages highlighting key areas on targeting mediators and suggesting relevant website content (for example, demo of TSSE, risk factors for skin cancer)	
			Playing an active role in early detection
		• 1 text: reminding participants about the 18-month survey	Self-efficacy re TSSE and asking HCP for skin exam
	• Study website	• Information about skin cancer risk among survivors, and the key role that skin self-examinations and early detection (ED) play	
			Knowledge/awareness
			Taking action
			**•** Risk perception: re cancer status
		• Information about how to conduct a self-examination and clinical images illustrating what to look for	
		• Information about how to ask a HCP for a skin exam:	**•** Barrier reduction
		Printable checklist	
		Guide to discussion	
		• Information about preventive behaviors	
		• Interactive skin exam quizzes	
		• Tips for making ED a priority	
		• Lay summaries of research on the efficacy of skin exams	
		• Videos and links to additional resources about skin cancer	
PAE + MD (Additional components/Mediators addressed)	• Physician activation packet	• Introduction letter describing intervention and encouraging MDs to do a full-body skin examination at the patient’s next visit	**•** Self-efficacy to perform a skin examination on the patient
		• Guide to conducting a full skin cancer examination	
		• Information about survivors’ increased risk of skin cancer	
		• Access to the provider section of the ASK website, which houses additional resources including clinical images illustrating what to look for	
	• Study website	• Information about skin cancer risk among survivors, and the key roles that skin exams and early detection (ED) play	**•** Barrier reduction related to HCP provision of skin examination (for example, how to do exam; how to identify suspicious lesions)
		• Video demonstration of how to conduct a thorough clinical skin examination	
		• Summaries of research on the efficacy of skin exams	
		• Videos and links to additional resources regarding skin cancer	
		• Access to all participant website materials	

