#### Economic impact measures

To estimate the economic impact of the intervention, at each assessment, we will examine participants’ visits with primary care providers and dermatologists, diagnostic procedures including biopsies and imaging, and treatment for newly-diagnosed skin conditions. This self-reported information will be verified and supplemented by data collected in chart reviews. We will use Medicare’s Direct Practice Expense and Resource Based Relative Value Scale (RBRVS) to estimate average unit costs for physician and laboratory services. A range of unit cost estimates will be evaluated in sensitivity analysis.

Our assessment of the downstream costs of the intervention, as well as the cost of the intervention itself, will allow performance of a limited cost-effectiveness analysis. We will estimate the cost per additional full-body skin cancer exam completed and the cost per additional skin cancer case detected, comparing the three intervention arms. The economic impact of the intervention will be evaluated using standard incremental cost-effectiveness analysis methods, and sensitivity analysis will be used to assess the impact of assumptions and uncertainty on results and conclusions [54,55].

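### The 18-month physician-exam item looks back only to month 6, so self-report misses exams in months 0–6 for participants who skipped the 12-month survey

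*Protocol article*

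**What the plan says.** Under Primary study outcomes, the protocol article lists "at least 1 physician skin examination prior to 18-month survey". No start of the window is stated; randomization to month 18 is the natural reading.

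Under Physician skin cancer examination, the schedule is: "Completion of a physician skin exam will be assessed at baseline, 12 months, and 18 months by participant report and chart review". The wording is the same each time: "At each assessment time point, participants will be asked" the question that begins "During the past 12 months, has your regular health care provider or your dermatologist carefully examined your whole body". It is answered yes or no, with a follow-up on whether the exam was routine or requested by the participant. The quoted item asks for no exam date.

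The same section says that self-report will be corroborated from the chart on a standard provider form. The paid record review is "to be completed after the participant completes his/her 18-month survey". Its look-back period is not given.

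Under Economic impact measures, the plan is: "We will estimate the cost per additional full-body skin cancer exam completed". Self-reported use of care at each assessment is to be checked and supplemented from charts.

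**The concern.** The outcome runs for 18 months, but the instrument used at the end of that period looks back 12. The two fit together only through the 12-month survey. The article states both the outcome and the wording of the item, so the mismatch is fixed in data collection. An analyst can decide later how to combine the two surveys, but cannot recover a self-report that was never asked for.

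A participant examined in month 3 who skips the 12-month survey and answers at month 18 can truthfully say no and be counted as unexamined. This moves participants with an exam into the no-exam group in every arm, lowers the observed rates and narrows the difference between arms.

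There is a smaller, opposite problem for the cost analysis. An exam in months 6–12 lies inside both look-back periods. Without dates, self-report cannot show whether two yes answers describe one exam or two.

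**Working it through.** **1. Look-back windows, in months since randomization**

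| Source | Covers |
|---|---|
| 12-month survey, on time | 0–12 |
| 18-month survey, on time | 6–18 |
| Both together | 0–18, overlapping in 6–12 |
| 18-month survey alone | 6–18; months 0–6 unseen |

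The look-back runs from completion of the survey. A 12-month survey returned at month 14, for example, covers months 2–14. With the 18-month survey it then leaves months 0–2 unseen. The article gives no return window, so this part cannot be sized.

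**2. The plan's own figures**

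Inputs from Power calculations: n = 200 per arm, 30% in the PAE arm, 15 points higher in at least one other arm, threshold 0.025, 2-df chi-squared test.

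Noncentrality: λ = n Σ(pᵢ − p̄)² / [p̄(1 − p̄)]. Critical value: 7.378.

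- 30/30/45%: p̄ = 0.35, λ = 200 × 0.015 / 0.2275 = 13.19, power 85.9%.
- 30/45/45%: p̄ = 0.40, λ = 200 × 0.015 / 0.24 = 12.50, power 83.7%.

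The stated 85% is reproduced. The recruitment target is too: 200 / 0.75 = 267 per arm, and 3 × 267 = 801.

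**3. Participants with an exam whom the 18-month item alone would miss**

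Assumptions: 30% and 45% are 18-month rates, exams occur at a constant rate, and chart review is ignored. The chance of an exam in months 6–18 is 1 − (1 − p)^(12/18).

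- p = 0.30: 1 − 0.70^(2/3) = 0.212. Missed: 0.088 / 0.30 = 29.5% of those with an exam.
- p = 0.45: 1 − 0.55^(2/3) = 0.329. Missed: 0.121 / 0.45 = 27.0%.

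**4. The loss confined to participants without a 12-month survey**

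Let m be the share of 18-month responders with no 12-month survey, taken as 10–25%, equal across arms and unrelated to having had an exam. The article gives no such figure. Observed rate = p − m × (missed part of p).

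| m | Observed, 30% arm | Observed, 45% arm | Misclassified among those with an exam | Power, one arm higher | Power, two arms higher |
|---|---|---|---|---|---|
| 0 | 30.0% | 45.0% | 0 | 85.9% | 83.7% |
| 10% | 29.1% | 43.8% | 2.7–2.9% | 84.7% | 82.2% |
| 25% | 27.8% | 42.0% | 6.7–7.4% | 82.7% | 79.9% |

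Over this range about 3–7% of those with an exam are misclassified. Power is about 80–85%, against 84–86% with complete capture.

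**The case against.** The strongest reply is that the measurement plan as a whole does cover months 0–6. The question is asked at month 12 as well, and chart review is a second source with no stated 12-month limit. How the two surveys are combined is a detail that a full protocol or SAP would normally settle.

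Much of this stands. Participants who return both surveys on time have no gap, and combining the reports may well be specified elsewhere. It does not help participants with no 12-month survey, because no analysis rule supplies an answer they were not asked for. Chart review may recover some early exams. However, it is described as corroboration, its look-back is unstated, and the Discussion accepts that some exams will not be documented.

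A reader might infer more than the documents support:

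- **A large loss of power.** This requires an analysis of the 18-month answer alone, which the article nowhere describes. It also requires reading 30% as an 18-month rate. If 30% and 45% are 12-month rates, which suits the baseline item, the 18-month item alone still measures 30% against 45% and power is as stated.
- **Selective loss of exams prompted by the physician packet.** The letter is for "encouraging MDs to do a full-body skin examination at the patient’s next visit", but no mailing date is given for it. The timing in Recruitment, "Within 7 days of randomization, each participant receives an enrollment packet", concerns the participant's own materials. Nothing shows that prompted exams cluster in months 0–6.
- **A biased comparison because 18 months is longer than the 12-month baseline window.** A constant 12-month rate of 30% could reach 1 − 0.70^1.5 = 41% over 18 months with no change in behaviour. That affects a before–after reading only. The planned test compares randomized arms over the same period.
- **Certain double counting of costs.** The item is yes or no, and chart data are to verify self-report. Double counting is possible, but not shown.

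**Conclusion.** The point holds as a modest gap in data collection. The 18-month item does not reach the start of the outcome period, and only the 12-month survey fills that gap in self-report. If 10–25% of 18-month responders lack the 12-month survey, about 3–7% of those with an exam are misclassified and power falls by roughly 1 to 4 percentage points, to about 80–85%. These figures rest on the assumed non-response share, a constant exam rate, 30% and 45% read as 18-month rates, and no recovery from charts. Any recovery from charts would make the loss smaller; late 12-month surveys would add to it by an amount the article does not allow one to estimate. The stated sample size and 85% power are correct as calculated.

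**What to change.** Add one item to the 18-month survey: *Since you joined the ASK study, has your provider or dermatologist carefully examined your whole body for skin cancer? If yes, month and year of each exam.*

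Define the outcome as an exam reported at the 12-month survey, at the 18-month survey or on this new item. Keep the past-12-months item for like-for-like comparison with baseline. Use the dates to remove from the cost analysis any exam in months 6–12 that both surveys report.

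The cost is one more question and a longer recall period for it. The article already lists recall bias as a limitation, so the 12-month reports should remain part of the definition and not be replaced by the new item.

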#### Reduced time interval

We used the following assumptions from the literature: mean wait time (time between call for appointment and actual appointment) of 38.2 days (95% CI = (35.4, 41.0) [49]. Based on the proportion of individuals with atypical moles and changing moles, we assume that for each of the study groups, there will be an estimated 60 to 75 participants per 267 in each group who will seek care from their primary physician or dermatologist in the 18-month period for a suspect skin lesion. A clinically significant improvement in reduction of time between the first finding of a suspect lesion and diagnostic visit would be between 14 and 21 days.

#### Mediating variables

We will also examine the impact of the intervention on key mediating variables hypothesized to be related to behavior change, including: risk perception related to one’s prior cancer status and risk of skin cancer, self-efficacy to perform a TSSE and to ask a physician to perform a complete skin examination, barriers (such as not knowing what types of moles or lesions to look for), demographics, skin cancer risk factors, skin cancer knowledge, attitudes toward TSSE, and detection awareness of basic warning signs of melanoma and BCCs [48,50-52]. In addition, we will test for interactions between these variables and the PAM, looking at subscales for risk perception, self-efficacy, barriers, and awareness [53].

#### Economic impact measures

To estimate the economic impact of the intervention, at each assessment, we will examine participants’ visits with primary care providers and dermatologists, diagnostic procedures including biopsies and imaging, and treatment for newly-diagnosed skin conditions. This self-reported information will be verified and supplemented by data collected in chart reviews. We will use Medicare’s Direct Practice Expense and Resource Based Relative Value Scale (RBRVS) to estimate average unit costs for physician and laboratory services. A range of unit cost estimates will be evaluated in sensitivity analysis.

Our assessment of the downstream costs of the intervention, as well as the cost of the intervention itself, will allow performance of a limited cost-effectiveness analysis. We will estimate the cost per additional full-body skin cancer exam completed and the cost per additional skin cancer case detected, comparing the three intervention arms. The economic impact of the intervention will be evaluated using standard incremental cost-effectiveness analysis methods, and sensitivity analysis will be used to assess the impact of assumptions and uncertainty on results and conclusions [54,55].

### Power calculations

Sample size considerations are based on an equal allocation of participants to intervention arms. Our primary outcome focuses on increases in both physician screening and skin self-examination; the prevalence of screening and expected effect sizes are derived from rates of physician screening in the CCSS population [32,56]. Similar increases for self-screening were found in a trial focused on skin self-examination amongst the siblings of melanoma patients conducted by Geller and Emmons [50]. Assuming that baseline physician screening rates are 30% across all randomization groups, a 10 to 15% increase in physician screening rates would be considered a clinically significant improvement. Based on an estimated 25% attrition rate by month 18, we propose recruiting 801 subjects who will be evenly divided across the 3 intervention groups. Using a main effects model, the design has at least 80% power to detect a 15% difference across any of the arms even if one takes a conservative 0.025 threshold for statistical significance. This is based on a 2-degree of freedom chi-squared test with n = 200 in each arm, assuming the screening rate in the PAE arm is 30% and at least one of the other arms is 15% higher. The actual power in this scenario is 85%. We will use a conservative 0.025 threshold to account for multiple comparisons.

In the unexpected case that the PAE-alone arm is found to be superior to the other 2 arms, we will have a number of mechanisms in place to study this from our baseline, 12- and 18-month surveys. In particular, we will be asking many questions on physician screening of the participants in all three conditions. It could be that participants are deterred by added involvement of their physicians, although the literature shows that physician prompts are some of the greatest influences in increasing screening behaviors. We will also have a series of questions specific to Arm 3 participants to test if there has been any part of the addition of the technology component that was off-putting (for example, some participants who are either overwhelmed, do not understand how to utilize it, or perhaps do not trust the transmission of their personal health information).

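### The claimed floor of 80% power (85% actual) holds only if the third arm sits at or very near one of the extremes; otherwise power for a 15-point difference falls to as low as 71%

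*Protocol article*

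**What the plan says.** All the relevant statements are in the Power calculations section of the protocol article.

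- The claim: "the design has at least 80% power to detect a 15% difference across any of the arms", even at the stricter significance threshold.
- The test and analysed size: "This is based on a 2-degree of freedom chi-squared test with n = 200 in each arm".
- The assumed rates: "assuming the screening rate in the PAE arm is 30% and at least one of the other arms is 15% higher".
- The result: "The actual power in this scenario is 85" per cent.
- The threshold: "We will use a conservative 0.025 threshold to account for multiple comparisons".
- Allocation and recruitment: "Sample size considerations are based on an equal allocation of participants to intervention arms", and "Based on an estimated 25% attrition rate by month 18, we propose recruiting 801 subjects".

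The rate in the third arm is not given here or anywhere else in the article.

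**The concern.** A 2-df chi-squared test compares three proportions at once. Its power depends on how all three spread around their mean, not only on the gap between the lowest and the highest. Fixing one arm at 30% and another at 45% therefore does not fix the power. A statement that power is at least 80% has to hold for every third-arm rate the scenario allows.

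The question matters because the three arms are cumulative: PAE, then physician activation added, then teledermoscopy added on top. If each added component contributes something to physician screening, the middle arm lies between the other two, and that is where a 2-df test is weakest for a given overall gap.

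At stake is the justification for recruiting 801 people. If the real figure is nearer 71%, the chance of missing a true 15-point difference is about 29%, not 15%, and a non-significant overall test could be over-read as evidence against an effect of that size.

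**Working it through.** **Inputs, all from Power calculations:** n = 200 analysed per arm, equal allocation, threshold 0.025, 2-df chi-squared test, PAE at 30%, one other arm at 45%, third arm m not stated. The sample size is consistent with the attrition allowance: 801 × 0.75 / 3 = 200.25 per arm.

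**Formula.** Power is the probability that a noncentral chi-squared variable with 2 df exceeds the 0.025 critical value, 7.378. The noncentrality is

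λ = n × Σ(pᵢ − p̄)² / [p̄(1 − p̄)]

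**Step 1: reproduce the stated 85%.**

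- Rates 30/30/45: p̄ = 0.35, Σ(pᵢ − p̄)² = 0.0150, p̄(1 − p̄) = 0.2275. λ = 200 × 0.0150 / 0.2275 = 13.19. Power 85.9% (simulation 85.5%).
- Rates 30/45/45: p̄ = 0.40, Σ(pᵢ − p̄)² = 0.0150, p̄(1 − p̄) = 0.2400. λ = 200 × 0.0150 / 0.2400 = 12.50. Power 83.7% (simulation 84.8%).

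An arcsine version gives 85.1% for both. The article's figure is therefore right when the third arm equals one of the extremes.

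**Step 2: put the third arm midway.**

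- Rates 30/37.5/45: p̄ = 0.375, Σ(pᵢ − p̄)² = 0.01125, p̄(1 − p̄) = 0.234375. λ = 200 × 0.01125 / 0.234375 = 9.60. Power 71.2% (simulation 71.4%, likelihood-ratio version 71.4%, arcsine version 71.7%).

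**Step 3: vary the third arm across 30% to 45%.**

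| Third arm | Power |
|---|---|
| 30% | 85.9% |
| 32% | 80.3% |
| 33% | 77.7% |
| 35% | 73.5% |
| 37.5% | 71.2% |
| 40% | 72.6% |
| 42% | 76.1% |
| 44% | 81.0% |
| 45% | 83.7% |

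The minimum is 71.1%, at about 37.8%. Power is under 80% from about 32.1% to about 43.6%, which is 11.5 of the 15 points in the range.

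**Step 4: what would give 80% throughout.** Keeping n = 200 and PAE at 30%, the difference between the extreme arms has to be about 16.5 points: at 30/38.25/46.5 power is 80.1%. Keeping 15 points instead, 240 analysed per arm are needed, which is 240 × 3 / 0.75 = 960 recruited.

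**Step 5: possible gain from a baseline covariate.** As an approximation, adjusting for a covariate correlated r with the outcome multiplies λ by 1/(1 − r²). The article gives no value for r, so 0.3 to 0.4 is an assumption. In the midpoint case:

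- r = 0.3: λ = 9.60 / 0.91 = 10.55, power 75.9%.
- r = 0.4: λ = 9.60 / 0.84 = 11.43, power 79.7%.

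**The case against.** The strongest defence is that nothing was miscalculated: 85% is correct for two legitimate configurations, and the article never mentions 37.5%. That is true. The defect is an unstated assumption about the third arm, presented as a guaranteed minimum.

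It can also be argued that the midpoint is not the expected pattern. The powered outcome is physician screening, physician activation goes to both enhanced arms, and the mediator that Table 1 lists for teledermoscopy is shorter waits for dermatology review. On that reading the rates would be close to 30/45/45, where power is 84–85%. Against this, the Arm 3 description says the report letters encourage dermatology referral for a clinical examination where necessary, so a further step in Arm 3 is possible. The article does not settle the matter. This means 71% should be read as the worst case within the range, not as the forecast. It does not rescue the floor, which has to hold for either pattern.

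Three numerical defences also fall short:

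- A single comparison of 30% with 45% at two-sided 0.025 has 80.7% power, but the article bases its claim on the 2-df test.
- At a 0.05 threshold the midpoint case has about 80% power, but the article commits to 0.025.
- A third arm outside 30–45% raises power (about 91% at 28%, 89% at 47%), but the largest gap is then 17 points or more, so this is no longer detection of a 15-point difference.

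Finally, the shortfall is modest, the design remains valid, and a null result should in any case be read from confidence intervals. That limits the consequence. It does not make the sentence correct.

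**Conclusion.** The concern holds. On the article's own test, sample size and threshold, power for a 15-point difference between the extreme arms runs from 71% to 86% depending on the third arm, and is under 80% over roughly three quarters of the 30–45% range (11.5 of 15 points). The quoted 85% is close to the best case within that range, not a lower bound.

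The conclusion rests on exactly 200 analysed per arm, PAE at 30%, the top arm at 45%, and a third arm somewhere between them. The 71% applies near the midpoint. With the third arm within about 1.5 to 2 points of either extreme, the 80% claim stands. Because the sentence supports the sample size, it should be corrected.

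**What to change.** Replace the power claim with wording such as: with 200 analysed per arm and a 0.025 threshold, the 2-df test has 71% to 86% power when the extreme arms differ by 15 points, depending on the rate in the third arm; 80% power whatever the third arm's rate requires a difference of about 16.5 points. If the 85% is kept as an example, state the third-arm rate behind it.

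In addition, include baseline physician-exam status as a covariate in the main-effects model. The Physician skin cancer examination section already has it collected at baseline. If its correlation with the outcome is 0.3 to 0.4 (an assumption), power in the midpoint case rises to about 76–80%. This narrows the shortfall but does not reliably close it, so the restated range is needed either way.

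The cost is one less favourable sentence and one model term. Recruitment, arms, outcomes and threshold are unchanged. Raising recruitment to 960 would also restore 80% at 15 points, but correcting the statement does not depend on it.
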